#### Functional Activity Questionnaire (FAQ)

It was designed by Pfeffer and is based on a previous study by the same autor [25, 26]. Assesses the ability to perform complex social activities, also known as instrumental activities of daily living. There are 11 items: managing money, shopping, making tea or coffee and turning off the appliance, preparing food, keeping abreast of community events, understanding and discussing radio and television news, reading magazines and books, remembering important dates, managing medication, traveling alone outside the neighborhood, greeting friends, and going out alone safely. Each item scores between 0 (normal) and 3 (totally dependent).

#### Dietary record for 3 days (one of them on the weekend) to know the individual intake [27]

Participants should write down the food and drinks eaten on each day, being as precise as possible. To facilitate said registration, a visual guide of food rations will be delivered and explained. Through the computer program "Food and health" (Institute of Nutrition and Food Technology of the University of Granada, Spain) the energy expenditure at rest, daily caloric needs, caloric intake, carbohydrates, proteins, lipids, fatty acids monounsaturated, polyunsaturated and saturated, fiber, vitamin B6, vitamin B12, vitamin D, folic acid, potassium, calcium, iron and iodine will be estimated. In addition to the portions of fruit and vegetables and vegetables during the 3 days.

#### Markers of inflammation

Interleukin 6 (IL-6), interleukin 1 (IL-1), interleukin 10 (IL-10), C-reactive protein and tumor necrosis factor (TNF-α) will be determined. (Thermo Fisher Scientific, 88–7066-88, 88–7261-22, 88–7106-22, KHA0031, KHC3011 respectively). The ELISA technique will be used to determine serum levels in serum samples obtained at visits. The blood will be collected in refrigerated tubes containing EDTA and the samples will be centrifuged at 2000 rpm at 4ºC. The sample will be separated into aliquots of approximately 0.5 ml for each determination in order to avoid thawing, freezing and the possible degradation of the sample proteins. Subsequently, they will be stored at -80ºC until the test is carried out.

#### Indicators of cardiovascular risk

Blood pressure and heart rate will be measured with the digital blood pressure monitor model M6 Omron Comfort (Omron Healthcare, Co., Ltd. Japan) validated according to the protocol of the European Society of Hypertension [28]. Anthropometric variables will also be measured, body weight with the clinically validated Omron BF511 body composition meter [29], height with the Seca 213 portable stadiometer with integrated leveler, and hip and waist circumference with a flexible tape measure.

### Intervention

#### Common intervention in both groups

All participants (control and intervention), before random assignment is made, and after the baseline visit, will receive brief nutritional advice (3 min) from one of the principal investigators, aimed at maintaining a balanced diet.

#### Specific intervention in the experimental group

Instructions will be given for the daily intake, in addition to the usual diet, of 50 g of raisins. The duration of this intervention will be 6 months. The variety of raisins for the study has been selected after analyzing the phenolic profile of 5 types of raisins (Corintio, Moscatel Argentina, Moscatel Málaga, Moscatel Chile and Sultanas). The raisin grape selected for the study was the Moscatel Málaga grape. The composition of polyphenols per 100 g of raisins is 1.98 mg of hydroxycinnamic acids, 13.49 mg of flavanols and 4.47 mg of flavonols. This represents a total of 19.47 mg of polyphenols per 100 g of Moscatel Málaga grape. The daily nutritional contribution of 50 g of grapes would be: 150 kcal; 0.25 g fat; 36 g of carbohydrates of which 14 g are from sugars; 1 g protein; 0.02 g of salt). Participants in this group will receive as many raisins as they need until the next replenishment visit.

### Structure and planning of visits

The principal investigators will contact the possible candidates recruited in the consultations of the health centers to participate in the study, and will arrange an interview in which the objective of the study will be explained to each participant, inviting them to sign the informed consent in case that they agree to participate. Each participant will have 2 visits: a baseline visit at the beginning of the study and another visit 6 months after the baseline visit. The duration of each visit will be approximately 90 min.

#### Baseline visit

Once the fulfillment of the selection criteria in each participant has been reviewed, the initial data will be collected, which will include sociodemographic data, personal and family history, use of medications and consumption of alcohol and tobacco. A physical examination will be performed and a plasma sample will be drawn to determine the laboratory data for the study. In addition, cognitive performance, physical activity, activities of daily living and quality of life will be evaluated. They will be given and explained how to make a dietary record for 3 days that they will later deliver. At the end of the baseline visit, random assignment will be made to one of the two study groups. People included in the intervention group will be given the amount of raisins that they will add to their usual diet for a month (1500 g per month). To facilitate the recording of the consumption of the raisins, each participant included in the intervention group will be given a diary/calendar in which they will write down the daily intake of the raisins (day and time). The control group will not receive any amount of raisins.

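### As the protocol is written, the first 3-day diet record is kept after dietary advice and unblinded allocation, and probably on raisin days in the raisin arm, so it is not a clean baseline for diet

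*Protocol article*

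**What the plan says.** All references are to the protocol article.

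- **Baseline visit**, on the diet form: "They will be given and explained how to make a dietary record for 3 days that they will later deliver". The same section continues: "At the end of the baseline visit, random assignment will be made to one of the two study groups". It then describes giving the intervention group one month of raisins (1500 g) and an intake diary.
- **Dietary record section**: the instrument is a "Dietary record for 3 days (one of them on the weekend) to know the individual intake".
- **Structure and planning of visits**: "Each participant will have 2 visits: a baseline visit at the beginning of the study and another visit 6 months after the baseline visit", and "The duration of each visit will be approximately 90 min". The section also mentions an interview at which consent is sought, without saying whether it is on a separate day.
- **Common intervention in both groups**: all participants, "before random assignment is made, and after the baseline visit, will receive brief nutritional advice".
- **Specific intervention in the experimental group**: the intervention lasts 6 months, and the daily 50 g portion supplies "150 kcal; 0.25 g fat; 36 g of carbohydrates", with 14 g of sugars and 1 g of protein.
- **Evaluation visits at 6-months**: these take place 6 months after the first visit and repeat the baseline measurements other than sociodemographic data.
- **Study variables** lists the energy and nutrient content of the diet as a secondary variable.
- **Statistic analysis** names diet among the variables for which every multivariable model is adjusted, without a time point.
- **Discussion** states that participants are not blinded.

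**The concern.** A baseline measurement should be complete before anything that differs between the arms can affect it. Here the form leaves the visit blank, and allocation is made before the participant goes home. The first record can then reflect the advice, knowledge of the allocated arm and, in the raisin arm, the raisins themselves.

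Two uses of the record are at stake.

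1. **Diet as an outcome.** Raisins in the first record shrink the measured change in energy and carbohydrate in the raisin arm. Raisins that were added to the diet could then look as if they had replaced other food. That distinction matters for interpreting weight and glycaemia.
2. **Diet as a covariate.** If the first record is the adjustment variable, the models condition on something that treatment may already have changed. The 6-month record has the same problem more plainly.

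**Working it through.** **Step 1. Order of events**

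| Event | Timing as stated | Section |
|---|---|---|
| Diet form given and explained | At the baseline visit | Baseline visit |
| Diet record completed | Over 3 days, one at a weekend; returned later | Dietary record; Baseline visit |
| Nutritional advice | After the baseline visit, before randomisation | Common intervention |
| Randomisation | End of the baseline visit | Baseline visit |
| First month of raisins | Described directly after randomisation | Baseline visit |
| Final visit | 6 months after the first visit | Evaluation visits at 6-months |

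A three-day record cannot be finished within about 90 minutes, and no separate randomisation visit is listed. Under the Baseline visit section, the record is therefore kept after randomisation. The advice comes before randomisation, so the record follows the advice too.

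The first raisin day is not given. A 6-month intervention and a final visit 6 months after the first imply a start close to the baseline visit. The supply of 1500 g / 50 g per day = 30 days fits a start at that hand-out. Nothing in the article holds back intake until the record is complete.

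One conflict remains. Advice given after the visit but before randomisation requires a gap between the two. Randomisation at the end of the visit leaves none.

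**Step 2. The protocol's energy figure**

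With the usual factors of 9 kcal/g for fat and 4 kcal/g for carbohydrate and protein:

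0.25 × 9 + 36 × 4 + 1 × 4 = 2.25 + 144 + 4 = 150.25 kcal

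This reproduces the stated 150 kcal per day.

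**Step 3. Effect on the diet-change comparison**

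Assume that raisins add to the diet without displacing food, that the full portion is eaten and recorded, that the 6-month record is kept while raisins are still being eaten, and that the advice shifts both arms equally. Let k be the number of recorded days in the first record that include raisins.

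Measured between-arm difference in change = 150 − 150 × k/3 kcal/day

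| k | Raisin energy in first record (kcal/day) | Measured difference in change (kcal/day) |
|---|---|---|
| 0 | 0 | 150 |
| 1 | 50 | 100 |
| 2 | 100 | 50 |
| 3 | 150 | 0 |

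With k = 3 the first record holds 3 × 50 = 150 g of raisins, 3 × 150 = 450 kcal, 3 × 36 = 108 g of carbohydrate and 3 × 14 = 42 g of sugars. The within-arm change in the raisin arm is diluted by the same 150 × k/3.

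**Step 4. Effect as a covariate**

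The article gives no standard deviation for energy intake. Assuming 300 to 600 kcal/day, the imbalance built in at k = 3 is d = 150/300 = 0.50 down to 150/600 = 0.25 SD. With 1:1 allocation the variance inflation of the treatment estimate is 1 + d²/4:

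- d = 0.50: 1 + 0.25/4 = 1.06
- d = 0.25: 1 + 0.0625/4 = 1.02

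Loss of precision is therefore small. The issue is possible bias from adjusting for a variable affected by treatment. Its size depends on how diet relates to each outcome, which the article does not give.

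**Step 5. Sample size**

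The SD of change is 4.75 × √(2 × (1 − 0.8)) = 3.00. For a 2-point difference with two-sided alpha 0.05 and 80% power this gives 36 per arm, and 36/0.9 = 40. The stated 40 per arm reproduces and is unaffected by this point.

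**The case against.** The best case for the plan has five parts.

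- **Raisin days are not documented.** The article states neither the recording days nor the first raisin day, and a start a few days late would still fit a nominal 6 months. This stands. A reader might infer that the record certainly contains the intervention; the text supports only that it probably does.
- **The advice section implies a gap before randomisation**, in which the record could be completed. Read alone it does, but the Baseline visit section contradicts it. This shows that the two sections need reconciling, not that the record is safe.
- **No diet change score is defined.** The analysis section plans comparisons of group means, and comparing 6-month intake between arms needs no baseline. This stands for that comparison. The planned within-group paired tests would still be diluted.
- **The covariate's time point and source are not stated.** Also true. A reader might infer that the cognitive and weight results are biased; that is possible but not shown, and no size can be computed. Still, neither the first nor the 6-month record is clearly free of treatment influence.
- **The contamination can be identified**, because foods are itemised and raisin intake is logged by day and time. This stands in part: subtracting raisins does not restore food they displaced, nor undo the advice.

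**Conclusion.** The concern holds in this form: followed as written, the plan provides no diet measurement that is clearly made before randomisation, for a named secondary variable that is also an adjustment variable. That the first record follows advice and allocation is the plain reading of the Baseline visit section. That it includes raisin days is a well-supported inference from the 6-month timeline.

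The loss in the measured diet change is anywhere from 0 to 150 kcal/day under the assumptions of step 3. Complete loss of the signal is the worst case, needing raisins on all three recorded days and full adherence; it should not be read as the expected result. Bias in diet-adjusted estimates is possible and of unknown size.

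The cognitive, laboratory and anthropometric measurements are taken at the visit before assignment, so those baselines are unaffected. The point deserves correction but does not threaten the unadjusted primary comparison.

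**What to change.** 1. **Reconcile the two sections** on when the advice and randomisation occur relative to the baseline visit, and state on which days the first diet record is kept.
2. **Have the record completed and returned before the advice and randomisation.** For example, give and explain the form at the consent interview, if that is held on an earlier day, and collect it at the baseline visit. The form is the same. The cost is at least three days, including a weekend day, between the two contacts. If the interview is on the same day as the baseline visit, the cost is one extra contact for participants over 70.
3. **Where this is not done, and for participants already enrolled**, do not call this record a baseline or use it as a covariate. Compare 6-month intake between arms, after confirming that the 6-month record is kept during the intervention period. Subtract recorded raisins from the first record only as a sensitivity analysis.
4. **State which diet measurement, if any, enters the adjusted models**, and restrict it to one made before randomisation. Items 1 and 4 cost only a change of wording.

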#### Resupply visits

They will only be performed in the intervention group, for the sole purpose of replenishing the raisins. During these visits, the raisin intake diary/calendar for the previous month will be collected and a new one will be delivered along with the corresponding raisins. This task will be carried out by a researcher who is not involved in the initial and 6-month interviews.

#### Evaluation visits at 6-months

They will be carried out 6 months after the first visit. The same variables will be collected as in the baseline visit except for sociodemographic data, already collected in the first visit.

### Statistic analysis

The results will be expressed as the mean ± standard deviation in quantitative variables or by frequency distribution in the case of qualitative variables. Normality will be evaluated using the Kolmogorov–Smirnov Test. In cases where a normal distribution cannot be assumed, the corresponding non-parametric tests will be used. The chi square test will be used to analyze the association between independent qualitative variables and the McNemar test for paired samples. Using the Student's t-test (Mann–Whitney U) for independent samples, the means between two groups will be compared, evaluating the change within the same group with the Student's t-test for paired data (Wilcoxon's test). The relationship between quantitative variables will be analyzed using Pearson's correlation coefficient (Spearman's correlation coefficient). A multivariate analysis will be carried out using different multiple linear and logistic regression models to analyze the effect of adding 50 g of raisins to the usual diet on the improvement of cognitive performance, on the modification of weight and body composition, blood pressure, glycaemia, in the improvement of the quality of life and changes in the markers of inflammation.

In all cases, it will be adjusted taking into account the variables that may influence the result, such as sociodemographic variables, those related to lifestyles (physical activity and diet, smoking status), drug use, the presence of comorbidity or the basal BMI, among others. For bilateral hypothesis tests, an alpha risk of 0.05 is set as the limit of statistical significance. The statistical program will be SPSS, v.26.0.

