### Sample size

The sample size was estimated taking into account the main variable of the study, the change in cognitive performance (categorical fluency). Accepting an alpha risk of 0.05 and a beta risk of 0.2 in a bilateral contrast, 40 subjects in the intervention group and 40 in the control group are needed to detect a difference equal to or greater than 2 points in the categorical fluency test. The common standard deviation is assumed to be 4.75 and a correlation coefficient between the initial and final measurement of 0.8. These estimates have been made based on contrasted data in the study by Garcia-Yu et al. [17]. Losses to follow-up of 10% have been estimated.

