### Recruitment

The assignment of participants to the intervention group (IG) or control group (CG). The allocation sequence will be generated by an independent researcher using the Epidat 4.2 program (Department of Health, Government of Galicia, Spain), with a ratio of 1/1. The assignment will remain hidden until the participants are assigned to each group.

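### A Kolmogorov–Smirnov test on the trial data decides whether the arms are compared on means or on ranks; one baseline-adjusted linear model for fluency should be fixed in advance

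*Protocol article*

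**What the plan says.** In the protocol article, Statistic analysis, normality is assessed by Kolmogorov–Smirnov, followed by the rule: "In cases where a normal distribution cannot be assumed, the corresponding non-parametric tests will be used". Each parametric test has a bracketed rank substitute: Mann–Whitney U for the two-sample t-test, Wilcoxon for the paired t-test, Spearman for Pearson. The two-sample pair is introduced as a comparison of means. The section does not say whether that comparison uses 6-month scores or changes.

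The same section plans linear and logistic regression for the effect of raisins on cognition and other outcomes. Its open-ended adjustment list names baseline BMI but not the baseline cognitive score. Neither the two-sample test nor the regression is named as the main analysis.

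The Sample size section works from "the main variable of the study, the change in cognitive performance (categorical fluency"), with 40 per group "needed to detect a difference equal to or greater than 2 points in the categorical fluency test". The Verbal fluency section defines this test as naming animals for one minute, so the score is a count.

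**The concern.** A primary comparison should be settled before the data are seen. Here a preliminary significance test on those data chooses between two procedures that answer different questions. The t-test addresses the difference in means, which is the scale of the 2 points. Mann–Whitney addresses whether values in one arm tend to exceed those in the other, and it gives no estimate of a mean difference. Calling both a comparison of means hides the change of target.

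The trigger also suits this endpoint poorly. Whole-number scores produce ties, and a normality test can reject because of the ties even when the underlying variable is normal. At stake are a predictable primary analysis and a result that can be read against the 2-point planning difference.

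**Working it through.** **Inputs (Sample size and Recruitment sections).** "Accepting an alpha risk of 0.05 and a beta risk of 0.2 in a bilateral contrast"; a difference of 2 points; "The common standard deviation is assumed to be 4.75 and a correlation coefficient between the initial and final measurement of 0.8"; allocation "with a ratio of 1/1"; "Losses to follow-up of 10% have been estimated".

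**Step 1: reproduce the plan's figure.** n per arm = 2 × (1.960 + 0.842)² × SD² / 2², with (1.960 + 0.842)² = 7.849 before rounding of the z values.

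- Change score: SD = 4.75 × √(2 × (1 − 0.8)) = 3.004. n = 2 × 7.849 × 9.025 / 4 = 35.4, so 36; 36 / 0.9 = 40. This matches the stated 40 per group.
- 6-month score adjusted for baseline: SD = 4.75 × √(1 − 0.8²) = 2.85. n = 2 × 7.849 × 8.1225 / 4 = 31.9, so 32; 32 / 0.9 = 35.6, so 36.
- 6-month score alone: SD = 4.75. n = 2 × 7.849 × 22.5625 / 4 = 88.5, so 89; 89 / 0.9 = 98.9, so 99.

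Of these three, only the change score gives 40, so the stated size already uses the baseline, by subtraction.

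**Step 2: power with 36 completers per arm.** Power = Φ(2 / (SD × √(2/36)) − 1.96). For the change score, 2 / (3.004 × 0.2357) = 2.824, and Φ(0.864) = 80.6%. For Mann–Whitney under normality, n is multiplied by 3/π, so 36 becomes 34.4. Two simulations (6000 and 3000 trials, scores rounded to whole numbers) check the formulas.

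| Analysis | Formula | Simulations |
|---|---|---|
| Linear model, 6-month score on group and baseline | 84.6% | 83%, 82% |
| t-test on change | 80.6% | 79%, 78% |
| Mann–Whitney on change | 78.8% | 77%, 77% |
| t-test on 6-month score | 43.1% | 42%, 43% |
| Mann–Whitney on 6-month score | 41.5% | 41%, 40% |

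On the same variable, t and Mann–Whitney differ by 1 to 2 points (3 in one run on 6-month scores). Moving from change to the 6-month score alone costs 80.6 − 43.1 = 37.5 points for the t-test and 78.8 − 41.5 = 37.3 for Mann–Whitney.

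**Step 3: how often the test switches.** Here the underlying scores are exactly normal and are rounded to whole numbers. Normality is checked in each arm of 36, and either rejection triggers the switch.

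- Lilliefors-type critical value, change scores: 44 to 46% of trials. This corresponds to 1 − √(1 − 0.45) = 26% per arm.
- Lilliefors-type critical value, 6-month scores: 25% of trials.
- Uncorrected Kolmogorov–Smirnov: about 1% of trials.
- The t-test and Mann–Whitney fell on different sides of 0.05 in 5% of trials.

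**Step 4: type I error of the two-stage rule on change scores.** It was 5.2% with normal residuals and 5.6% with exponential (skewed) residuals. The Monte Carlo standard error is √(0.05 × 0.95 / 6000) = 0.3 points. In the skewed case 99% of trials switched and Mann–Whitney alone also gave 5.6%, so the slight excess does not come from the pre-test. With the same skewed residuals, the t-test on change gave 5.1% and the baseline-adjusted model 5.3%. Neither needed a rescue rule at this sample size.

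**The case against.** The strongest reply is that the switch does little harm. Type I error holds, and with normal data the power cost is about 1 to 2 points. With strongly skewed residuals the rank test does better: in the exponential case Mann–Whitney on change had 92% power, against 79% for the t-test and 83% for the baseline-adjusted model. The planned linear regression already gives a mean difference and can carry the baseline. The Kolmogorov–Smirnov variant and the variable checked are details that a condensed article may leave to the full protocol or SAP. All of this stands, and it limits the size of the point. It does not remove the rule that the article itself states, or its description of both tests as comparing means.

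Three stronger readings are tempting, and the documents do not support them:

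- A reader might infer that the rank fallback cannot use the baseline. It can be run on change scores, and the trial is sized on change.
- A reader might infer that falling back to ranks roughly halves the power. That drop, to about 40–43%, comes from testing 6-month scores without the baseline, and it hits the t-test equally.
- A reader might infer that precision is lost whenever the fallback is triggered. The skewed case shows the opposite can happen.

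**Conclusion.** The point holds in limited form. The article lets the data choose between a mean comparison and a rank comparison. For a count such as fluency, that choice ranges from almost never switching (about 1%) to switching nearly half the time (about 45%), depending on an unstated variant of the test. The consequence is an unsettled primary test and target, not an invalid one: type I error is not materially inflated and the direct power cost is about 1 to 2 points.

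It is worth correcting because a better choice is available from data already collected. The baseline-adjusted linear model gains about 4 points over the change-score t-test (84.6 − 80.6 by formula; 82–83% against 78–79% in simulation).

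These figures assume the plan's SD of 4.75 and correlation of 0.8, equal SDs, 36 completers per arm, rounding to whole numbers, normal residuals except where stated, and a normality check made separately in each arm.

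**What to change.** Delete the normality-driven switch for the between-group comparison. State as the primary analysis a linear model of 6-month categorical fluency on randomised group and baseline fluency, reporting the adjusted mean difference with its 95% CI at two-sided 0.05. Use the same baseline-adjusted model for the other quantitative outcomes. Keep Mann–Whitney on change scores as a named sensitivity analysis, described as a comparison of ranks and not of means.

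A log scale for the inflammation markers, fixed in advance, is optional; its small downside is that effects are then reported as ratios.

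The cost is wording only. Linear regression is already a planned method and the baseline scores are already collected. The model needs 32 completers per arm, or 36 randomised with 10% losses, so 40 per arm is enough. If a separate SAP already fixes the primary model, the article's rule should be aligned with it.

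### The analysis section does not commit to the between-arm comparison of change in categorical fluency on which the 80% power was calculated

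*Protocol article*

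**What the plan says.** Under Sample size, the protocol article names "the main variable of the study, the change in cognitive performance (categorical fluency") as the variable that fixes the numbers. The error rates are set by "Accepting an alpha risk of 0.05 and a beta risk of 0.2 in a bilateral contrast", and the result is that "40 subjects in the intervention group and 40 in the control group are needed" for a target effect of at least 2 points on this test. The SD is given as 4.75 and common to both measurements, and the calculation also uses "a correlation coefficient between the initial and final measurement of 0.8", with 10% loss to follow-up.

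Under Statistic analysis, the t-test sentence (with Mann–Whitney and Wilcoxon as fallbacks) reads "the means between two groups will be compared, evaluating the change within the same group" by the paired test. The section then plans "different multiple linear and logistic regression models" for the effect of the raisins on improvement in cognition and on a list of other outcomes. These models are adjusted for sociodemographic and lifestyle variables, drug use, comorbidity, baseline BMI and unspecified others. The baseline value of the outcome is not among the covariates named, and no analysis is designated as primary.

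**The concern.** The sample size depends on removing stable between-person differences in fluency. That is what the correlation of 0.8 does in the calculation. The analysis section should therefore fix a between-arm analysis that uses the baseline score, either by comparing change or by adjusting for baseline. As written, the between-arm t-test is attached to means and the word change to the paired test within each arm. The regression could close the gap, but its named covariates include baseline BMI and not the baseline outcome, the one covariate whose correlation the sizing relies on.

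Two things are at stake. First, the choice left open moves power from about 80% to about 42%. Second, paired tests within each arm do not estimate the effect of the raisins. Fluency is tested twice, so both arms might gain from repetition. A significant gain in the raisin arm beside a non-significant one in the control arm could then be read as a treatment effect when there is none.

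**Working it through.** **Inputs (protocol article, Sample size).** Difference 2 points; SD 4.75; correlation r = 0.8; two-sided alpha 0.05; power 80%; loss 10%; 40 per arm. The SD is taken to be the same at both visits, as the word common implies.

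**1. Reproducing the plan's figure.**
- SD of change = 4.75 × √(2 × (1 − 0.8)) = 3.004.
- n per arm = 2 × (1.960 + 0.842)² × SD² / 2² = 2 × 7.849 × 3.004² / 4 = 35.4, so 36 evaluable.
- 36 / 0.9 = 40 randomised per arm. This matches the stated number exactly.

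**2. Would another analysis also give 40?** The same formula with other SDs:

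| Between-arm analysis | SD used | n evaluable | n after 10% loss |
|---|---|---|---|
| 6-month means, baseline unused | 4.75 | 88.5 → 89 | 99 |
| Change from baseline | 3.004 | 35.4 → 36 | 40 |
| ANCOVA on baseline, 4.75 × √(1 − 0.8²) | 2.85 | 31.9 → 32 | 36 |

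Of these three, only the comparison of change yields 40.

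**3. Power with 36 completers per arm (40 × 0.9).** The non-centrality parameter is 2 / (SD × √(2/36)), and power comes from the non-central t distribution:

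| Between-arm analysis | Non-centrality | Power |
|---|---|---|
| 6-month means | 1.79 | 42.2% |
| Change from baseline | 2.82 | 79.5% |
| ANCOVA on baseline | 2.98 | 83.6% |

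The normal approximation gives 43.1%, 80.6% and 84.5%. By the t-based calculation, a comparison of 6-month means would need about 90 completers per arm for 80% power.

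**4. Within-arm tests when the raisins do nothing.** The documents give no practice effect, so this step rests on an assumed gain common to both arms. With a gain of 1 point, change SD 3.004 and 36 per arm, each paired test is significant with probability 0.493. The raisin arm is then significant and the control arm not with probability 0.493 × (1 − 0.493) = 0.25. For a common gain of 0.5 or 1.5 points the figure is about 14%. The product p(1 − p) cannot exceed 0.25, so the 1-point case is the worst case.

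**The case against.** The strongest reply is that the two sections, read together, already deliver the planned power. Sample size defines the main variable as a change, and an independent-samples t-test applied to that variable is exactly the test that was sized. Statistic analysis also goes on to plan regression of the raisin effect on improvement in cognition, which is a between-arm analysis. The covariate list ends openly, so it does not exclude the baseline score, and with change as the outcome the planned power does not need it. A condensed article may also leave exact model terms to a fuller document.

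Most of this stands. A reader might infer that the trial tests change only within arms, or that it has about half its stated power. The documents support neither. The regression is a between-arm analysis, and nowhere does the article say that raw 6-month means are what the t-test compares. Nor does it say that paired tests will serve as evidence of efficacy, so the 25% in the working illustrates a risk and does not describe the plan.

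A reader might also infer that every logistic model here would dichotomise a continuous score. That goes too far: quality of life is among the listed outcomes, and the EuroQol section describes severity levels by dimension, which are categorical.

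What the reply does not remove is the mismatch in what the article does state. Its only sentence on change in the bivariate plan concerns the within-arm test, its named covariates leave out the outcome's own baseline, and nothing says which analysis answers the primary question.

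**Conclusion.** The point holds in limited form. The sample size is arithmetically sound for a between-arm comparison of change in categorical fluency, and the analysis section permits that comparison without committing to it. At 36 completers per arm and a true difference of 2 points, power is about 80% on change, about 84% with baseline-adjusted ANCOVA, and about 42% on raw 6-month means. The last figure is conditional on a reading that the article leaves open and should not be quoted as the power of the trial. All three rest on the article's own SD of 4.75, correlation of 0.8 and 10% loss. The advantage of using the baseline depends on that correlation being realised. ANCOVA over change is a modest gain of about four percentage points. The larger benefit of the fix is that it closes off the low-power reading and stops within-arm tests from standing in for the treatment effect.

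**What to change.** In Statistic analysis, name one primary analysis: a linear model of the 6-month categorical fluency score on randomised arm and baseline categorical fluency, reporting the adjusted between-arm difference with its 95% CI. Use the same form of model, each with its own baseline value, for the other quantitative outcomes. State that paired tests within each arm are descriptive and will not be taken as evidence of effect. Restrict logistic regression to outcomes that are categorical as measured.

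The cost is wording only. Cognitive tests are already done at the baseline visit, the planned software fits the model, and the 40 per arm can stay, since ANCOVA needs 36 per arm after 10% loss on the same assumptions.
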